### The implementation

The intervention will be introduced in a staged way across an entire hospital using a stepped wedge design [54,55] described in more detail in the next section. The implementation of the intervention will be facilitated by a nurse paired with a hospital dietitian. The four nurse leads will be identified prior to the project commencing and their wards will be allocated to one of the four groups using stratified randomisation. For three of the four groups an additional five hospital wards will be randomly assigned to the group; the last group will be assigned an additional six wards meaning that a total of 25 wards are allocated (Table 1). Allocation of wards to groups will be conducted (by author TS) by coding each ward and using a random number generator (MS-Excel) to select codes for each groups. The intervention will be implemented over a two month period across all six wards within a group but staggered sequentially every three months between groups. Control sites will experience usual hospital care until the intervention is delivered. The intervention will be carried out over 12 months, commencing in March 2011.

**Table 1 T1:** Representation of stepped wedge trial design showing four groups and five measurement time periods incorporating control (O) and intervention (X) phases

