### Sampling

The primary outcome data will be collected on a sample of patients from only one ward per group due to resource constraints. Given that the median length of stay in the hospital is only 4–5 days, and our requirement is to collect weight data over at least a 1 week period, we will purposively sample a ward that is most likely to care for patients who have a length of stay in excess of 7 days. To further minimise the number of patients for whom a weight on admission is collected but who are discharged before 7 days, patients with Diagnostic Related Groups (DRGs) known to have longer than average length of stay will be targeted. The following patients will be excluded from body mass measurement: those undergoing palliation or expected to die within a month, those undergoing amputation or surgical removal of large tumours, those admitted directly to the intensive care unit or with stays in intensive care of more than 3 weeks. A total of 20 patients for each of four wards will be weighed on each of five measurement periods, resulting in a total sample size of 400. Whilst it was desirable to include either more wards or more patients per ward (see power calculations in Analysis) in the sample, resource constraints limited the final sample size available for analysis. Given the size of the wards (typically 20–24 patients each) it is anticipated that it may take repeated weekly visits over an entire month to reach a total sample of 20 patients with body weight measurements for each sampling period. Patients whose length of stay exceeds 14 days will be weighed at day 14 and day 21 to allow calculation of change in weight over the first, second and third weeks of their admission. The second and third week data will both be analysed separately.

Secondary outcomes and hospital process measures will only be collected from the records of patients included in the primary outcome sample, described above. Written consent to weigh patients will not be sought because it is routine practice and part of usual care in the hospital.

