### Analysis

Analysis of stepped wedge designs is challenging [54]. The unidirectional aspect of stepped wedged trials complicates analysis because the treatment effect cannot be estimated exclusively from within-cluster comparisons [59]. Analytical techniques depend on a number of factors including: the existence of a temporal effect on the outcome, equality or inequality in cluster size, and normality of continuous data. Based on a design using equal cluster sizes, and assuming that there will be a temporal effect, linear mixed models (LMM) will be used [65]. If there are no temporal effects, then within-cluster analysis can be used to estimate the treatment effect. Random effects will be used to model correlation between individuals within the same cluster and measure the variance of individuals in a cluster and variance at the cluster-level [59]. Hussey et al. (2007) provide equations and worked examples for calculating both the within-cluster and between-cluster calculations [59].

We conducted power analysis based on a sub-set of body weight data collected at baseline at four hospital wards. In their first week of admission, the prevalence of patients with (i) BMI greater than or equal to 20 who lost 2 or more kg, and (ii) BMI less than 20 who lost 1 kg or more, was measured as 26.7%. Using equations seven and eight [59], a coefficient of variation $\left(\frac{\tau }{\mu }=\frac{0.056}{0.267}\right)$of 0.21, with four groups of 20 patients measured over five time periods totalling 400 patients, a power of 80% would detect a reduction in the prevalence of weight loss from 26.7% to 6.5%, ie a 75% reduction. If a smaller effect size is selected, such as a reduction in prevalence from 26.7% to 16.5% (a 38% reduction), the power is reduced to 29%.

It is also possible to calculate the required sample size for an adequately (80%) powered study. To detect a smaller effect size (a 38% reduction in proportion of patients experiencing weight loss), the total sample size required is 1800 patients, comprising 90 patients in each of four groups measured across the five time periods. Alternatively, although not feasible for reasons defined above, if all 25 wards were included in the sample and 20 patients were included from each ward at each of five time periods, the resulting study comprising a total of 2,500 patients would have a power of 69% to detect a 38% reduction in proportion of patients experiencing weight loss.

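### A random ward variance estimated from four measured wards makes the planned mixed model's usual z test too liberal: about 7% to 8.5% false positives instead of 5% under the protocol's own power assumptions

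*Protocol article*

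**What the plan says.** Twenty-five wards are randomised to four groups, but patients are measured on far fewer. The Sampling section states: "The primary outcome data will be collected on a sample of patients from only one ward per group due to resource constraints". That ward is chosen purposively, as one likely to hold patients who stay more than seven days. The size follows: "A total of 20 patients for each of four wards will be weighed on each of five measurement periods, resulting in a total sample size", namely 400 patients. The same section takes secondary outcomes and hospital process measures from the same patients only.

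For the analysis, a linear mixed model is planned because a temporal effect is expected. On the ward term the Analysis section says: "Random effects will be used to model correlation between individuals within the same cluster and measure the variance of individuals in a cluster", and it also wants the variance at cluster level. All outcomes except the Alberta Context Tool are to be analysed by the stepped wedge design, in Stata. The section does not say whether estimation is by ML or REML, whether tests use z or t, or whether a small-sample correction applies.

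On power: "We conducted power analysis based on a sub-set of body weight data collected at baseline at four hospital wards". With a ward SD (tau) of 0.056 around 26.7%, "with four groups of 20 patients measured over five time periods totalling 400 patients", the section gives 80% power for a fall from 26.7% to 6.5%, and 29% for a fall to 16.5%.

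**The concern.** A mixed model with a random ward intercept uses two sources of information on the intervention effect: change within wards, and differences between wards in the same period. The estimated ward variance sets how much weight the between-ward part gets. With four wards that estimate is very imprecise and is often zero. When it is zero, the model treats ward differences as pure patient-level noise and reports a standard error that is too small. A z test makes no allowance for this.

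At stake is the credibility of a positive result. The protocol openly accepts low power, but that is a different weakness: low power makes true effects hard to find, whereas a liberal test makes false ones easier to find. The protocol expects its results to inform a larger study, so a spurious signal would have consequences. Treating the wards as random draws is also hard to defend when they were picked for long stays.

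**Working it through.** **Inputs.** Four wards and 20 patients per ward and period (Sampling); five periods and the one-way crossover pattern (Table 1); p0 = 0.267 and tau = 0.056 (Analysis). Alpha is not stated; two-sided 0.05 is assumed because it reproduces the stated power.

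**Step 1: the plan's own power.** The closed-form stepped wedge variance, with I = 4 wards, T = 5 periods and cell variance s² = 0.267 × 0.733 / 20 = 0.009786, is

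Var = I s² (s² + T tau²) / [(I U − W) s² + (U² + I T U − T W − I V) tau²].

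Table 1 gives U = 10, W = 30, V = 30, so the bracket is 10 s² + 30 tau². With tau² = 0.003136:

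- Numerator: 4 × 0.009786 × (0.009786 + 0.01568) = 0.000997
- Denominator: 0.09786 + 0.09408 = 0.1919
- SE = √(0.000997 / 0.1919) = 0.0721
- Fall of 20.2 points: Φ(0.202/0.0721 − 1.96) = 80% (stated 80%)
- Fall of 10.2 points: Φ(0.102/0.0721 − 1.96) = 29% (stated 29%)

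Both reproduce, with tau entered as a known constant and a normal reference distribution.

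**Step 2: how well four wards determine tau.** Even if the four ward means carried no sampling error, 3 degrees of freedom give a 95% interval for tau of 0.056 × √(3/χ²), that is 0.032 to 0.209. In simulated trials with true tau = 0.056, the REML estimate of tau has a 2.5% to 97.5% range of 0 to 0.126. It is exactly zero in 27% of trials (ML: 41%).

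**Step 3: type I error.** The 4 × 5 × 20 design was simulated with no effect and no secular trend, fitted with fixed periods, the intervention indicator and a random ward intercept, and tested at |z| > 1.96 (20,000 trials at tau = 0.056 on binary data, 8,000 for the other rows).

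| True value | REML | ML |
|---|---|---|
| Binary, tau = 0 | 4.9% | 5.2% |
| Binary, tau = 0.03 | 6.3% | 7.1% |
| Binary, tau = 0.056 | 7.1% | 8.4% |
| Binary, tau = 0.10 | 7.4% | 8.8% |
| Normal, ICC 0.016 | 7.1% | 8.4% |
| Normal, ICC 0.05 | 7.4% | 9.1% |
| Normal, ICC 0.20 | 5.8% | 6.5% |

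An ICC of 0.016 corresponds to tau = 0.056: 0.003136 / (0.1957 + 0.003136). The normal rows matter because the primary outcome is a rate of change in body mass and BMI. With all 25 wards measured, the same model gives 5.5% to 5.6%, so the inflation comes from the number of wards.

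**Step 4: alternatives on the same data.** Fixed effects for ward and period at patient level give 5.1%. If wards also vary from period to period (an assumption; the protocol gives no figure), this model is inflated too: about 7% at a ward-by-period SD of 0.04 and 8% to 9% at 0.056. The random-ward z test then reaches 9% to 12%. An analysis of the 20 ward-period means, with 20 − (5 periods + 3 ward contrasts + 1 intervention) = 11 degrees of freedom, stays at about 5% in all these cases.

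**Step 5: power of the alternatives.** On simulated binary data at tau = 0.056 without ward-by-period variation, fixed wards give about 86% and 28% for the two effects. Cell means give about 80% and 24% to 25%.

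**The case against.** The strongest objection is that the inflation belongs to an uncorrected z test, which the article never names. Estimator and degrees-of-freedom method are details an article may leave to a full analysis plan, and REML with a small-sample correction would be compatible with the text. This stands as a condition on the size of the problem. It does not remove the point: the article itself pairs four measured wards with an estimated ward variance, and that model fitted in the usual way is liberal.

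It is also fair that the protocol calls its results preliminary and admits that it can detect only large effects. It nowhere mentions a liberal test.

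Three stronger readings are tempting and are not supported:

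- A reader might infer that true power is only 71% and 24%. Those values follow from letting tau grow without bound in the formula: SE = √(4 × 0.009786 × 5/30) = 0.0808. But they keep the control variance in every cell. At 6.5% the binomial variance is 0.065 × 0.935 = 0.061, against 0.196 at 26.7%, and binary simulation with fixed wards gives about 86% and 28%.
- A reader might infer that every stepped wedge outcome is affected. The inflation vanishes near tau = 0 and is small at an ICC of 0.20, and the article gives no ICC for the other outcomes.
- A reader might say that the ward variance cannot be estimated. It is identifiable; it is only very imprecise.

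**Conclusion.** The point holds as a weakness of the stated model. With four measured wards, a random ward intercept and z-based inference, a nominal 5% test has a true size of about 7% (REML) to 8.5% (ML) at the protocol's own inputs, on binary and continuous data alike. This rests on tau near 0.056 (or an ICC of roughly 0.016 to 0.05 for a continuous outcome), two-sided alpha of 0.05, and no small-sample correction. Outside that range the inflation is smaller; with ward-by-period variation it is larger.

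The power statement is arithmetically correct under the equations it cites. Its limitation is that it treats as known a tau taken from a subset of baseline data on four wards. On the same constant-variance formula, power for the larger effect runs from about 90% at tau = 0 to about 71% as tau grows, so the dependence on tau is real but bounded.

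**What to change.** For outcomes measured on the four wards, fit ward (four levels) and period (five levels) as fixed effects with the intervention indicator, use t-based inference, and limit conclusions to these purposively chosen wards. Add the analysis of the 20 ward-period means on 11 degrees of freedom, because the patient-level fixed-ward model is itself liberal if wards vary from period to period. If a random ward effect is kept, specify REML with a small-sample degrees-of-freedom correction.

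State that the 80% and 29% treat tau as known, and recompute power for the chosen model. On binary data the figures to expect are about 86% and 28% with fixed wards, or about 80% and 24% to 25% with cell means; ward-by-period variation would lower the cell-mean figures.

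The cost is a changed model specification and no extra data. Some power is lost relative to the random-ward model, and the inference no longer extends to wards in general.

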**Methods/Design:**

A pragmatic stepped wedge randomised cluster trial with repeated cross section design will be conducted. The unit of randomisation is the ward, with allocation by a random numbers table. Four groups of wards (n = 6 for three groups, n = 7 for one group) will be randomly allocated to each intervention time point over the trial. Two trained local facilitators (a nurse and dietitian for each group) will introduce the intervention. The primary outcome measure is change in patient’s body weight, secondary patient outcomes are: length of stay, all-cause mortality, discharge destinations, readmission rates and ED presentations. Patient outcomes will be measured on one ward per group, with 20 patients measured per ward per time period by an unblinded researcher. Including baseline, measurements will be conducted at five time periods. Staff perspectives on the context of care will be measured with the Alberta Context Tool.

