### Outcomes

The primary patient outcome measure will be the rate of change in body mass and body mass index over weekly periods from admission to discharge. Body mass (kg) will be measured to the nearest 0.1 kg, between 0800 and 1200 and post bladder voiding. Depending on patient mobility this may require a standing, sitting, bed or sling weighing machine. Patient’s height (cm) will be measured to the nearest 0.1 cm using a stadiometer or predicted from measured ulna length depending on patient mobility. Body mass index (kg/m^2^) is calculated as body weight divided by height squared. The body mass data will be collected by a researcher (LL), who is not blinded to the randomisation schedule.

Secondary patient outcome measures will include: length of stay, all cause mortality, discharge destination (to a higher, lower or equivalent level of care), number and duration of re-admissions (defined as an unplanned admission within 28 days of discharge related to the primary admission [62] (3, 6, 12 months post-discharge), and number of Emergency Department (ED) presentations (3, 6, 12 months post-discharge). The re-admission and ED presentations data will be collected from across all five major public hospitals in the metropolitan region using the State’s patient record systems, which will also provide length of stay, discharge destination and mortality, cross-referenced with State death registries. The collector of the secondary patient outcome data will be blinded to the randomisation schedule.

The staff-related outcome is nurse perspectives of context of care as assessed by administration of the Alberta Context Tool (ACT) [63,64] before the intervention.

Hospital process-related outcomes include: compliance to using the MUST tool on all patients, compliance to using additional food supplements when indicated, compliance to using the red tray system when indicated and compliance to documenting patient’s foods and fluids intake by nurses. The hospital process measures will be obtained through medical record review.

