Finally, although the project was originally envisaged as accessing routinely collected [54] patient body mass data, initial investigation of this dataset indicated systematic biases and large gaps rendering it unfit for this purpose. Therefore we decided to prospectively collect body mass data on a targeted sub-section of the population. This approach has introduced limitations related to power, as the study will be under-powered to detect anything but large effect sizes, and in generalisability, as we will purposively sample from the patient population and target those with a length of stay likely to be at least 1 week. However, as we are anticipating the results from this study to be preliminary in nature, and to potentially inform a larger study, this was necessary as the first step towards investigating the multifaceted intervention. Further embedding of nutrition screening and weighing of patients will provide a data source for future studies evaluating long term sustainability of the intervention.

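### The stated power belongs to a binary week-1 weight-loss proportion that is not a listed outcome, so no power figure applies to the continuous primary outcome

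*Protocol article*

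**What the plan says.** **Primary outcome.** The Abstract (Methods/Design) states: "The primary outcome measure is change in patient’s body weight". The Outcomes section states: "The primary patient outcome measure will be the rate of change in body mass and body mass index over weekly periods from admission to discharge". Both are continuous; the second adds BMI and refers to weekly periods.

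**Periods.** Under Sampling, patients with longer stays are weighed again at days 14 and 21 "to allow calculation of change in weight over the first, second and third weeks of their admission". The section adds: "The second and third week data will both be analysed separately".

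**Model.** Under Analysis: "assuming that there will be a temporal effect, linear mixed models (LMM) will be used".

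**Power.** The same section bases its power on a week-1 proportion: patients losing at least 2 kg if BMI is 20 or above, or at least 1 kg if BMI is below 20. The baseline value is 26.7%. It then says that "a power of 80% would detect a reduction in the prevalence of weight loss from 26.7% to 6.5%, ie a 75% reduction". It gives 29% power for a fall to 16.5%, and 1800 patients as the size needed for 80% power at that smaller effect.

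**Acknowledged limit.** The Discussion says "the study will be under-powered to detect anything but large effect sizes".

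**The concern.** A power statement should describe the test that will decide the primary question. Here the outcome being tested and the outcome being powered differ in kind. One is a mean change in kg or kg/m² per week; the other is the share of patients crossing a threshold that depends on BMI. The thresholded share is not among the primary, secondary, staff or process outcomes. For the continuous change, the article gives no SD, no target difference and no power.

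Two things are at stake. First, readers are told a detectable effect that does not belong to the planned analysis, and the Discussion's statement about large effects has no other calculation behind it. Second, the Discussion presents the study as preliminary to a possible larger one. The 1800-patient figure could be carried into that study although it applies to a different endpoint.

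A smaller matter is that the Abstract, Outcomes and Sampling do not name the primary variable and period in the same way, so it is not clear which single quantity the power should refer to.

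**Working it through.** **Inputs from the article.** Four measured wards, five periods, 20 patients per ward-period (400 in total), the design in Table 1, p = 0.267, τ = 0.056. Alpha is not stated; two-sided 0.05 is assumed, and it reproduces the stated powers.

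**Formula** (stepped-wedge variance with a random ward effect and fixed periods):

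Var = I·s²·(s² + T·τ²) / [(I·U − W)·s² + (U² + I·T·U − T·W − I·V)·τ²]

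Power = Φ(|d|/SE − 1.96)

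From Table 1: I = 4, T = 5, U = 10, W = 0 + 1 + 4 + 9 + 16 = 30, V = 16 + 9 + 4 + 1 = 30. Hence I·U − W = 10, and U² + I·T·U − T·W − I·V = 100 + 200 − 150 − 120 = 30.

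**Step 1: reproduce the plan's figures (binary).**
- s² = 0.267 × 0.733 / 20 = 0.009786; τ² = 0.003136.
- Var = 4 × 0.009786 × (0.009786 + 0.01568) / (0.09786 + 0.09408) = 0.005193, so SE = 0.0721.
- 26.7% to 6.5%: 0.202 / 0.0721 = 2.80, power 80.0% (stated 80%).
- 26.7% to 16.5%: 0.102 / 0.0721 = 1.42, power 29.3% (stated 29%).
- With 90 per ward-period (1800 patients): SE = 0.0366, power 79.5% (stated 80%).

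These figures are arithmetically sound for the binary measure. The further 69% figure for all 25 wards is also worded for the proportion. The same formula gives 94.5% there, but that is a separate question and is not used here.

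**Step 2: the same design with a continuous change (illustration).** Assume normally distributed change, a single threshold, a common shift and total SD = 1. Then s² = (1 − ICC)/20 and τ² = ICC. The ICC implied by the plan's own inputs is 0.003136 / (0.003136 + 0.1957) = 0.016. Values up to 0.10 are assumed.

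Shift for 26.7% to 16.5%: z(0.267) − z(0.165) = −0.622 + 0.974 = 0.352 SD. Detectable shift at 80% power: (1.96 + 0.842) × SE.

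| ICC | SE | Power for 0.352 SD | Shift detectable at 80% |
|---|---|---|---|
| 0.016 | 0.162 | 58.6% | 0.453 SD |
| 0.05 | 0.169 | 54.9% | 0.474 SD |
| 0.10 | 0.169 | 55.1% | 0.472 SD |

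Worked line for ICC 0.016: Var = 4 × 0.0492 × (0.0492 + 0.08) / (0.492 + 0.48) = 0.02616; SE = 0.1617; 0.352 / 0.1617 − 1.96 = 0.218; Φ = 58.6%.

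**Step 3: back to prevalence.** Φ(−0.622 − 0.453) = 14.1% and Φ(−0.622 − 0.474) = 13.7%, so about 14% against the stated 6.5%. Part of this gap arises because the plan uses the control-rate variance throughout. With the variance at the mean of the two rates, the binary test reaches 80% power at about 9%. The rest comes from dichotomising.

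**Step 4: in kg.** The article gives no SD. At ICC 0.016 the detectable difference would be 0.45, 0.91 or 1.36 kg for an assumed SD of 1, 2 or 3 kg.

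**The case against.** The strongest reply is that the mismatch does little harm. Resource limits fixed the sample at 400, the article already calls itself under-powered and preliminary, and on the illustration above the binary calculation is conservative. A corrected figure would change no procedure and no sample size. All of this stands, and it lowers the weight of the point. It does not remove it, because the stated detectable effect still belongs to a quantity that is not an outcome.

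A second reply is that a statistical analysis plan may supply the missing detail. It may, and the absence of an alpha level or a testing hierarchy is not held against the article. But the article itself sets out one outcome and powers another.

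A third is that a linear mixed model can be fitted to a binary variable or to ward proportions. It can, but the proportion would then have to appear under Outcomes.

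A reader might also infer that there are six co-primary tests (two variables by three weeks) with an inflated false-positive rate. The text does not say that. The Abstract names body weight alone. The Sampling sentence on weeks 2 and 3 can be read as setting them apart from a main week-1 analysis, and both the sampling aim of at least one week and the power data point to week 1. BMI change is weight change divided by a fixed height squared, so it adds little separate error. What remains is a request to make the three sections agree.

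**Conclusion.** The point holds as a mismatch of endpoints. The 80%, 29% and 1800-patient figures are correct for a thresholded week-1 proportion and do not describe the continuous primary outcome, for which no power is stated. This should be fixed, but it does not threaten the design.

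Under the stated assumptions, one continuous test has about 55-59% power where the article gives 29%, and it detects about 0.45-0.47 SD (prevalence about 14%) where the article gives 6.5%. These values are illustrative. The article's threshold differs by BMI, the ICC for weight change is not given, and normality and a common shift are assumed.

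It would be wrong to conclude that the trial is weaker than claimed: for a single continuous test the article probably understates its power. Nor is there an arithmetic error in the three figures reproduced here.

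**What to change.** Choose one of two routes.

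1. **Continuous primary.** Name one variable and one period, in the same words, in the Abstract, Outcomes and Sampling. Week-1 change in body mass fits the Abstract, the sampling aim and the baseline data. Make BMI change and weeks 2 and 3 secondary. Recompute power with the same formula, using the SD and between-ward variance of week-1 weight change from the baseline data already collected, and state the target difference in kg. Replace the current power and sample-size figures, and check the Discussion's sentence on power against the result.
2. **Binary primary.** List the thresholded week-1 proportion as the primary outcome under Outcomes and in the Abstract, and specify an analysis for a binary variable. The 80%, 29% and 1800-patient figures can then stay.

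The first route costs wording changes and one recalculation from data in hand; the second costs wording changes and a revised analysis statement. Neither needs more patients or a change in data collection.

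### The stated power and sample-size figures are for an unlisted yes/no weight-loss measure, so power for the continuous primary outcome is not stated and cannot be judged from the plan.

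*Protocol article*

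**What the plan says.** The Outcomes section of the protocol article defines a continuous primary outcome: "The primary patient outcome measure will be the rate of change in body mass and body mass index over weekly periods from admission to discharge". Weights are recorded to 0.1 kg. The Abstract agrees, naming change in body weight. For the analysis, "assuming that there will be a temporal effect, linear mixed models (LMM) will be used".

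The power calculation in the Analysis section uses a different variable. It classifies each patient's first week as a loss or not, with a cut-off of 2 kg when BMI is at least 20 and 1 kg when it is lower. The prevalence comes from baseline data on four wards; the definition ends "BMI less than 20 who lost 1 kg or more, was measured as 26.7"%. The between-ward SD is 0.056, a coefficient of variation "of 0.21, with four groups of 20 patients measured over five time periods totalling 400 patients". Three results concern us:

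- 80% power: "a power of 80% would detect a reduction in the prevalence of weight loss from 26.7% to 6.5%, ie a 75% reduction".
- A smaller effect: "such as a reduction in prevalence from 26.7% to 16.5% (a 38% reduction), the power is reduced to 29"%.
- 1,800 patients (90 per group per period) for 80% power at that smaller effect.

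This yes/no measure is not among the primary, secondary, staff or process outcomes. The Sampling section refers the reader to these calculations, and the Discussion accepts a power limitation, "as the study will be under-powered to detect anything but large effect sizes".

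**The concern.** A power statement should describe the analysis that will be reported as primary. Here every power and size figure concerns a proportion, while the primary analysis estimates a mean change in kg. The article gives no SD, no intraclass correlation and no detectable difference on the kg scale, so the printed figures cannot be carried over.

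This is not a detail that a condensed article might leave to a fuller document. The article sets out its power calculation at length, but for a variable that it does not list as an outcome.

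Two uses of the figures are at stake. One is reading a null result on weight change, where the relevant quantity is the detectable difference in kg. The other is planning the larger study that the Discussion hopes to inform. Neither can rest on 80%, 29% or 1,800 if the outcome is continuous weight change.

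**Working it through.** **Inputs from the Analysis and Sampling sections.** Four wards, five periods, n = 20 per ward and period (400 in all); control prevalence p = 0.267; between-ward SD τ = 0.056. **Assumption:** two-sided 5% test, since the article states neither level nor sidedness.

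**Formula.** This is the stepped-wedge (Hussey-Hughes) variance, with fixed period effects and a random ward intercept. Table 1 of the article gives I = 4, T = 5, U = 4+3+2+1 = 10, W = 0+1+4+9+16 = 30 and V = 16+9+4+1 = 30. Hence IU − W = 10 and U² + ITU − TW − IV = 100+200−150−120 = 30, so

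Var = 4s(s + 5τ²) / (10s + 30τ²), where s = patient variance / n, and power = Φ(effect/SE − 1.96).

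**Step 1: reproduce the printed figures.** With s = 0.267 × 0.733 / 20 = 0.009786 and τ² = 0.003136, SE = 0.0721.

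| Scenario | Effect | n per cell | Power found | Printed |
|---|---|---|---|---|
| 26.7% to 6.5% | 0.202 | 20 | 80.0% | 80% |
| 26.7% to 16.5% | 0.102 | 20 | 29.3% | 29% |
| 26.7% to 16.5% | 0.102 | 90 (1,800 patients) | 79.5% | 80% |

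Reaching a full 80% in the last row takes 92 per cell, or 1,840 patients, so 1,800 is within about 3%. The arithmetic is right for the yes/no measure.

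**Step 2: what the continuous analysis needs.** Working in patient SD units, s = 1/20 = 0.05. The ward variance is not given for kg change. As an assumption, carry over the ratio from the yes/no measure: τ² = 0.003136 / 0.1957 = 0.0160, an intraclass correlation of about 0.016. Then Var = 4 × 0.05 × (0.05 + 0.0801) / (0.5 + 0.4807) = 0.0265, so SE = 0.163 SD.

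The size of effect that corresponds to 26.7% falling to 16.5% depends on the shape of weight change and on who benefits. The article gives neither, so a range is shown. The calculation also treats the two BMI-dependent cut-offs as a single cut, which is a simplification.

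- *Normal change, every patient shifted equally.* The standard normal quantiles are −0.622 and −0.974, a shift of 0.352 SD. Power = Φ(0.352/0.163 − 1.96) = 58%. If the shift is expressed in within-ward SD (0.352/√(1 − 0.0158) = 0.355), power is 59%. Patients needed for 80% power: about 720 to 740.
- *Heavy tails, equal shift.* For a t distribution with 5 df the shift is 0.318 SD and power 50% (about 920 patients). With 3 df it is 0.265 SD and power 37% (about 1,360).
- *Benefit only to would-be losers, who then resemble non-losers.* For a normal variable, losers and non-losers differ on average by φ/(p(1−p)) = 0.3288/0.1957 = 1.680 SD. Moving 10.2% of patients shifts the mean by 0.102 × 1.680 = 0.171 SD. Power = Φ(0.171/0.163 − 1.96) = 18% (about 3,400 patients).

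The intraclass correlation matters too. Under the uniform normal shift of 0.352 SD, power is 70% at a correlation of 0 and 51% at 0.10.

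**The case against.** The strongest reply has four parts.

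**The figures are correct and labelled.** This stands. They reproduce, and the Analysis section speaks of prevalence and proportions throughout. The fault is a mismatch of endpoint, not of arithmetic, and readers are not told that the figures describe mean change in kg.

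**The sample size did not come from this calculation.** This also stands. Sampling and Discussion both say that resources set the size, and the Discussion calls the expected results preliminary. No design choice at 400 patients turns on the figures, which limits the consequence to interpretation and later planning.

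**The Discussion's caution may survive.** Even under the uniform normal shift, 80% power requires a 0.456 SD shift, which corresponds to 26.7% falling to about 14%, a relative reduction of roughly 47%. That is still a large effect. The sentence on power is therefore not shown to be wrong.

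**The direction of the error is unknown.** A reader might infer that, because dichotomising discards information, the printed figures are too pessimistic, that sensitivity is understated about two-fold, and that a follow-on study would be sized some 2.5 times too large. The documents do not support this. It needs near-normal change and the same shift in every patient. The intervention directs supplements to patients found at risk and red trays to those needing full feeding assistance, so a uniform shift is not assured. If only would-be losers benefit, power falls below the printed 29%.

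**Conclusion.** The point holds as an endpoint and power mismatch. The printed 80%, 29% and 1,800 apply to a first-week yes/no measure that is not a listed outcome, and no power is stated for the continuous primary outcome.

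The size of the discrepancy cannot be fixed from the documents. For the scenario printed at 29%, the illustrative cases at an intraclass correlation of 0.016 run from about 18% to about 59%, so even its sign is open. These values rest on a two-sided 5% test, an intraclass correlation borrowed from the yes/no measure, and assumed shapes for weight change and benefit. They show that the printed figures do not transfer; they are not estimates of the trial's power. The matter should be corrected, but it does not threaten the design.

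**What to change.** 1. From the baseline weights already collected on four wards, take the patient SD and ward SD of weekly change in kg. Restate in the Analysis section, with the same equations, the power and the detectable difference in kg for the continuous primary outcome. With four wards the ward SD will be imprecise, so show a range for it, and state the test level and sidedness.
2. Keep the present figures only as figures for weight-loss prevalence. Either list that prevalence in the Outcomes section as a secondary outcome, with its cut-offs, or stop using it as the basis for the trial's power.
3. Revisit the Discussion's sentence on power only if the recalculated figures call for it.

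The cost is a short recalculation on existing data and a few sentences. It needs no more patients and no change of design.
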